**Method::**

We designed a pilot multicenter, randomized, parallel controlled trial. This trial aims to test the feasibility of carrying out a large-sample clinical trial. In this trial, 50 eligible patients with aMCI will be included and allocated to acupuncture group (n = 25) or sham acupuncture group (n = 25) at random. Subjects will accept treatment 2 times a week for 12 weeks continuously, with a total of 24 treatment sessions. We will select 6 acupoints (GV20, GV14, bilateral BL18, bilateral BL23). For the clinical outcomes, the primary outcome is Montreal cognitive assessment, which will be assessed from baseline to the end of this trial. And the secondary outcomes are Mini-mental State Examination, Delayed Story Recall, Clinical Dementia Rating scale, Global Deterioration Scale, Activity of Daily Life, Alzheimer Disease Assessment Scale-Cognitive Section, brain magnetic resonance imaging, brain functional magnetic resonance imaging, and event-related potential P300, which will be assessed before and after treatment. In addition, we will assess the safety outcomes from baseline to the end of this trial and feasibility outcome after treatment. We will evaluate neuropsychological assessment scale (Montreal cognitive assessment, Mini-mental State Examination, Alzheimer Disease Assessment Scale-Cognitive Section) at 3 months and 6 months after treatment.

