### Feasibility

2.12

In order to evaluate the feasibility of carrying out RCTs with large samples in the next stage, we set the following indicators in this pilot trial. The feasibility outcomes are demonstrated in Table 3.

**Table 3 T3:** Feasibility outcomes.

Feasibility outcomes	Evaluation criteria
1. Proportion of participants who completed the required 12-week acupuncture treatment and cognitive rehabilitation training program	If ≥80% participants completed, proceed; if 50%–80% participants completed, modify protocol; if <50% participants completed, do not proceed.
2. Proportion of participants who completed a 12-week aerobic exercise program	If ≥80% participants completed, proceed; if <80% participants completed, modify protocol.
3. Rate of drop-out during treatment	If rate of drop-out ≤20%, proceed; if rate of drop-out is 20%–50%, modify protocol; if rate of drop-out <50%, do not proceed.
4. Response rate	Response rate of subjects to the collected indicators will be evaluated at pre-therapy, posttherapy, 3 months and 6 months after treatment.
5. Blinding test	All the participants will be tested for the success of blinding after the final treatment session. They will be asked to judge whether they have received real acupuncture or sham acupuncture.
6. Satisfaction	Participants’ satisfaction with the intervention will be ranked on a 5-point scale, each point is very satisfied, satisfied, neutral, dissatisfied, and very dissatisfied.
7. Average number of eligible subjects recruited in each center per month	Each center separately counts the number of eligible participants.
8. Enrollment rate	Proportion of participants who were last included in the study among all eligible participants.

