### Sample size

2.13

Based on the RCT report published by Jiang et al^[43]^ in 2016, the sample size was estimated with MoCA as the main outcome. After 12 weeks of treatment, the difference of MoCA between pre-therapy and posttherapy in the conventional rehabilitation group (without acupuncture) was 2.83 ± 1.13, and that of MoCA between pre-therapy and posttherapy in acupuncture group was 1.33 ± 1.20. The test level was set at *α* = 0.05 and *β* = 0.1. By comparing the differences between 2 independent samples, PASS 2008 software was used to calculate that the required sample size of each group was 13 cases, and 26 cases in both groups.

To sum up, considering that the follow-up loss rate is 20%, the sample size should be 26/(1 – 0.2) = 33 cases. Considering that we have enough research capacity to fulfill the expected research tasks, we intend to expand the sample size to a total of 50 cases, 25 cases in each group.

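### The drop-out stop rule in Table 3 has its inequality reversed: drop-out below 50% meets the stop clause, and drop-out above 50% meets no clause

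*Protocol article*

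**What the plan says.** The abstract gives the purpose of the pilot: "This trial aims to test the feasibility of carrying out a large-sample clinical trial". Section 2.12 (Feasibility) lists the indicators for that purpose in Table 3. Items 1 to 3 carry numeric thresholds. Of these, only items 1 and 3 can lead to a decision not to proceed.

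Item 3, on drop-out during treatment, has three clauses:

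- "If rate of drop-out ≤20%, proceed"
- "if rate of drop-out is 20%–50%, modify protocol"
- "if rate of drop-out <50%, do not proceed"

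Item 1 is the corresponding rule on completing the 12-week acupuncture and cognitive training programme. It reads "If ≥80% participants completed, proceed; if 50%–80% participants completed, modify protocol", followed by "if <50% participants completed, do not proceed".

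Section 2.13 (Sample size) fixes the planned number: "we intend to expand the sample size to a total of 50 cases, 25 cases in each group". No other part of the article restates or corrects the drop-out rule.

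**The concern.** High drop-out is the bad outcome, so the bands of item 3 should run upwards from proceed, through modify, to stop. The first two do. The third drops back and takes in everything under 50%. It looks as if the stop clause of item 1 was carried over without turning the sign: below 50% is a sensible stop for completion and the reverse of one for drop-out.

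What is at stake is the go/no-go decision. Applied literally, the item tells the team both to proceed and not to proceed when retention is good, and tells them nothing when more than half the participants leave. If the clause is reinterpreted only once the drop-out rate is known, the progression criterion has in effect been chosen after seeing the data, which is what setting it in advance is meant to prevent.

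**Working it through.** The disputed figure is a decision threshold, so there is no formula to reproduce. The check is to apply the printed clauses to every possible result.

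**Inputs.** Denominator N = 50 (section 2.13). Clauses of item 3 (Table 3): proceed if r ≤ 20%; modify if 20% ≤ r ≤ 50%; do not proceed if r < 50%, where r = k/50 and k is the number of drop-outs.

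**As printed.**

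| Drop-outs k | Rate | Clauses met |
|---|---|---|
| 0–9 | 0–18% | proceed and do not proceed |
| 10 | 20% | proceed, modify and do not proceed |
| 11–24 | 22–48% | modify and do not proceed |
| 25 | 50% | modify only |
| 26–50 | 52–100% | none |

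The counts add up as 25 (k = 0–24, contradictory) + 1 (k = 25, clear) + 25 (k = 26–50, no verdict) = 51.

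Three examples: 5/50 = 10% meets proceed and do not proceed; 15/50 = 30% meets modify and do not proceed; 30/50 = 60% meets nothing in item 3.

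**Which direction was meant.** Suppose every participant either completes treatment or drops out, so that drop-out = 100% − completion. Item 1 then translates as follows:

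- completion ≥ 80% becomes drop-out ≤ 20%: proceed;
- completion 50%–80% becomes drop-out 20%–50%: modify;
- completion < 50% becomes drop-out > 50%: do not proceed.

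The first two lines match item 3 exactly. Only the third differs, and only in its sign.

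**With the sign reversed (> 50%) and nothing else changed.** k = 0–9 gives proceed; k = 10 gives proceed and modify; k = 11–25 gives modify; k = 26–50 gives do not proceed. Every count now has a verdict. The only overlap left is at exactly 20%, which the first two clauses share.

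**The case against.** The strongest reply is that the intent is obvious and the harm small. The ascending sequence and the matching item 1 show what was meant, and nobody would abandon the programme at 5% drop-out when the same line says proceed. The slip touches no treatment, randomization, data collection or estimate in the pilot itself.

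Two more specific points also have force. First, a participant who drops out during treatment cannot have completed it, so on the same denominator drop-out above 50% means completion below 50%, and item 1 then says stop. At 30/50 lost, completion is at most 20/50 = 40%. The statement that nothing is triggered is therefore true of item 3 alone, not of Table 3 as a whole. Second, section 2.13 plans for 20% loss ("considering that the follow-up loss rate is 20%, the sample size should be 26/(1 – 0.2) = 33 cases"), which is exactly the rate at which all three clauses apply. That figure is a follow-up loss rate, however, and the article does not say that all of it falls within the 12 treatment weeks. It is an indication, not the expected count for this rule.

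Both points stand as limits on the consequences. Neither repairs the item. Item 1 covers the gap at the high end but leaves the contradiction from 0 to 24 drop-outs untouched, and the article gives no rule for combining the items when they disagree. That a reader can guess the intended sign makes the correction easy; it does not make the printed criterion usable. Nor is this a detail left to a fuller plan: the article states a numeric rule, and states it wrongly.

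**Conclusion.** The concern holds. Item 3 of Table 3 is wrong as written. With N = 50 it gives contradictory verdicts for 25 of the 51 possible drop-out counts, no verdict for another 25, and a single verdict only at exactly 25 drop-outs. Low drop-out does not produce a clean stop; it meets the stop clause alongside proceed, modify or both.

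The mapping takes all 50 planned participants as the denominator. A different number would shift the counts but not the percentage bands. That item 1 acts as a backstop above 50% further assumes the same denominator for both items. Because this is one of only two rules that can stop progression, in a pilot whose stated aim is feasibility, it should be corrected before it is applied.

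**What to change.** Rewrite item 3 of Table 3 with bands that neither overlap nor leave a gap:

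- drop-out ≤ 20%: proceed;
- drop-out > 20% and ≤ 50%: modify protocol;
- drop-out > 50%: do not proceed.

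With 50 participants this gives 0–10, 11–25 and 26–50 drop-outs. In the same edit, tidy the 80% endpoint that two bands of item 1 share: ≥ 80% proceed, 50% to < 80% modify, < 50% do not proceed.

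Section 3.1 (Trial status) reports the trial as underway, so the correction should be dated and recorded, preferably before drop-out is tabulated. The cost is a line of text in one table; sample size, procedures and data collection do not change.

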### Sample size

2.13

Based on the RCT report published by Jiang et al^[43]^ in 2016, the sample size was estimated with MoCA as the main outcome. After 12 weeks of treatment, the difference of MoCA between pre-therapy and posttherapy in the conventional rehabilitation group (without acupuncture) was 2.83 ± 1.13, and that of MoCA between pre-therapy and posttherapy in acupuncture group was 1.33 ± 1.20. The test level was set at *α* = 0.05 and *β* = 0.1. By comparing the differences between 2 independent samples, PASS 2008 software was used to calculate that the required sample size of each group was 13 cases, and 26 cases in both groups.

To sum up, considering that the follow-up loss rate is 20%, the sample size should be 26/(1 – 0.2) = 33 cases. Considering that we have enough research capacity to fulfill the expected research tasks, we intend to expand the sample size to a total of 50 cases, 25 cases in each group.

### Randomization and allocation concealment

2.14

The stratified random allocation operation of experimental group and control group will be completed by the researcher of the Clinical Research Center, South China Research Center for Acupuncture and Moxibustion, Guangzhou University of Chinese Medicine. The programming and randomized operation will be performed by PROC PLAN of SAS 9.2. The results of random allocation will be distributed through the central random allocation system in the internet.

### Blinding

2.15

Patients will be notified that they will be received acupuncture treatment or acupuncture-like simulation treatment, which is randomly allocated. And they will be required to close their eyes during treatment. Only the acupuncturists will be aware of the detailed grouping. Subjects and other investigators (like data analysts, outcome evaluators, and statisticians) will not know group assignments. All investigators will receive trial training before the study starts to ensure the success of the implementation of blind method.

### Blinding test

2.16

All subjects will be tested for the success of blinding after the final treatment session. They will be asked to judge whether they have received real acupuncture or sham acupuncture. In the scale of 0 to100, 0 is “confirmed to be sham acupuncture”, 100 is “confirmed to be real acupuncture”. After scoring, the results will be collected and statistically analyzed by the research team. The blinding success assessment scale is shown in Figure 4.

**Figure 4 F4:**

Blinding success assessment scale.

### Safety and adverse events

2.17

If participants are considered to have undesirable effect after acupuncture treatment, they should discontinue treatment and tell acupuncturists. Acupuncturists will diagnose and cure the AE, and other investigator will contact them to fill in the AE form and AE record log. AEs may occur during acupuncture, such as fainting, hematoma, bent needle, stuck needle, broken needle, infection, etc. If any relevant AE occurs during the study, it will be dealt with immediately.

Participants and acupuncturists should report all of the AEs (include all discomfort, symptoms, or illness occurring during the study). All detailed information of AEs (include occurrence time, symptoms, duration, severity, treatment measures, and duration) will be reported in the case report forms (CRFs). In case of serious AE, it will be reported to the lead unit and the state administration of traditional Chinese medicine within 24 hours. One week after symptomatic treatment, follow-up will be conducted through outpatient service, telephone, or visit. We will analyze the impact of all AEs after this trial finishes.

### Data management

2.18

All data will be input into a pre-designed, password protected dataset by someone who will not know the group assignment. In order to protect the subjects’ privacy, we will adopt codes and initials to mark the subjects’ personal information. Specified investigators will monitor the quality of online CRFs completion. Only outcome evaluators can access CRFs and will carry out double-data entry with any amendment or transformation of written data in subjects’ CRFs documented and dated. The clinical supervisor will monitor the data and study progress at least once a day.

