#### Sham-acupuncture group

2.9.5

Subjects in this group will accept sham acupuncture and conventional treatment. The needles will not insert into the skin, and acupoints are the same as test group. A non-invasive placebo control, namely sham blunt-tip needle, will be used in this trial. The base of Park Sham Device will be adhered to the skin of the acupoint. We will insert the sham needle into the tube and tap the needle tip to make the needle touch the acupoint skin but not pierce the skin. The needle on BL18 and BL23 will be connected to a HANS-200E sham electroacupuncture apparatus without electrical pulse. Needles will be also retained for 30 minutes before removing.

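### Outcome evaluators who must stay blind are given CRF access and the data entry, while the same CRFs hold adverse-event detail that could reveal the arm for some patients

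*Protocol article*

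**What the plan says.** Four sections of the protocol article bear on this.

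- **2.15 Blinding:** "Subjects and other investigators (like data analysts, outcome evaluators, and statisticians) will not know group assignments". Only the acupuncturists are to know the allocation.
- **2.17 Safety and adverse events:** "AEs may occur during acupuncture, such as fainting, hematoma, bent needle, stuck needle, broken needle, infection, etc". Full details of each AE, including symptoms, severity and how it was treated, "will be reported in the case report forms". An investigator other than the acupuncturist completes the AE form and log.
- **2.18 Data management:** "Only outcome evaluators can access CRFs and will carry out double-data entry". The same section has a person unaware of allocation enter all data, adds that "Specified investigators will monitor the quality of online CRFs completion", and has a clinical supervisor monitor the data at least daily.
- **2.9.5 Sham-acupuncture group:** "The needles will not insert into the skin, and acupoints are the same as test group". In the acupuncture group (2.9.4) needles go in to 15 to 25 mm and are manipulated by hand.

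Section 2.21 keeps efficacy raters out of treatment delivery. It says nothing about keeping them away from AE records.

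**The concern.** The plan sets up a blind rating team and then makes that team the handlers of the records most likely to disclose the arm. MoCA, MMSE and ADAS-cog are administered by a rater, so a rater's belief about the arm can influence administration and scoring.

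Rater blinding carries much of the protection here. The Discussion concedes that acupuncturists cannot be blinded and that some participants may guess their arm. The blinding test in 2.16 questions participants only, so an unmasked rater would not be detected. Because the trial is a pilot for a larger one, the access rule could also be carried forward.

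**Working it through.** The plan gives no figure on this point, so the check mainly sets the sections side by side.

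1. **Must evaluators be blind?** Yes. Section 2.15 names them.
2. **Do the CRFs hold AE detail?** Yes, under 2.17.
3. **Do evaluators reach the CRFs?** Yes. Section 2.18 gives them access and assigns them double data entry.
4. **Does AE content point to an arm?** It depends on the event:
   - Stuck, bent or broken needle: hardly to be expected with a blunt needle that stays outside the skin, so strongly suggestive of the acupuncture arm.
   - Hematoma: suggestive but not conclusive.
   - Fainting: not specific to an arm.
   - Infection: not specific, because 2.17 collects any illness during the study.
5. **Could this come before a rating?** Yes. Needling runs over the 12 treatment weeks. Table 1 places the post-baseline MoCA, MMSE and ADAS-cog ratings at 12 weeks and at the 3- and 6-month follow-ups. The article does not say when evaluators read or enter AE pages. Entry after a patient's last rating would remove the risk, but nothing requires it.
6. **Is there a barrier elsewhere?** The article states none between AE pages and outcome pages, or between raters and data-entry staff.

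**Scale, by assumption only.** Let p be the proportion of the 25 acupuncture patients with an arm-revealing AE on the CRF. The documents give no value for p. The expected number is 25 × p, and the chance of at least one is 1 − (1 − p)^25, taking patients as independent.

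| Assumed p | Expected patients | Chance of at least one |
|---|---|---|
| 2% | 0.5 | 40% |
| 5% | 1.25 | 72% |
| 10% | 2.5 | 93% |
| 20% | 5 | 99.6% |

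At the lower assumed rates, few patients are exposed, though it is quite possible that at least one is. The table counts patients whose records could unmask a rater. It does not measure bias. The sample size in 2.13 is unaffected.

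**The case against.** The strongest reply has four parts.

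- **Page-level permissions are normally set in a data-management plan, and this is a condensed article.** This stands in part: the article does not say whether access is restricted by page. But the access rule itself is stated, and as worded it covers the CRFs without exception. The point rests on that statement.
- **The rule may be meant to protect blinding by keeping acupuncturists out of the CRFs.** That is a fair reading of its purpose. It does not remove the evaluators' access.
- **Nothing says that the evaluator who enters a patient's AE later rates that patient.** This stands. Section 2.21 describes an assessment team, and 2.17 has another investigator complete the AE form. The unmasking is therefore a possibility that the rule allows.
- **The trial is a pilot and few patients would be affected.** This limits the weight of the point, but the remedy is cheap.

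A reader might infer from 2.18 that evaluators are literally the only people with CRF access. The documents do not support that, since the same section gives investigators and a supervisor monitoring roles. A reader might also count every AE listed in 2.17 as a sign of the acupuncture arm. Fainting and infection are not.

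**Conclusion.** The point holds as a risk created by a stated rule. Sections 2.17 and 2.18 together could unmask raters of MoCA, MMSE and ADAS-cog, contrary to 2.15, for the probably few patients with a telling AE. This assumes that at least one such AE occurs and that an evaluator sees the entry before rating that patient. The documents neither establish nor exclude either condition.

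The effect on the treatment comparison cannot be quantified. A reader might be tempted to size it as the shift in the acupuncture-arm mean, (k/25) × s, where k is the number of unmasked patients and s is the rater's shift in MoCA points:

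- k = 2 and s = 1 gives 0.08 points.
- k = 8 and s = 2 gives 0.64 points.

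Against the difference of 2.83 − 1.33 = 1.5 points in 2.13, these are 5% and 43%. Neither k nor s has any basis in the documents, and the upper figure takes the extreme of both. No such percentage should be reported as a finding.

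**What to change.** In section 2.18:

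1. Let outcome evaluators open and complete only their own outcome pages.
2. Close AE, treatment and session pages to anyone who rates outcomes, at least until that patient's last rating.
3. Have those pages entered by existing staff who do not rate. Two candidates for the double entry are the investigator who fills in the AE form under 2.17 and the blinded data-entry person in 2.18. The text must say that neither is a rater, because at present it does not.
4. Reconcile 'only' with the investigators and supervisor who monitor CRFs and data, by listing each role and the pages it may open.

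The cost is a change of user permissions, a few sentences in 2.18 and a small shift of data-entry work among existing staff. The change will not stop a participant from telling a rater what he or she felt during treatment.

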### Statistical analysis

2.19

The statistical tests involved in this study will include unilateral and bilateral tests with a significance level of alpha = 0.05. Statistical analysis will be completed by SPSS 22.0 software (International Business Machines Corp., Armonk NY).

Effect analysis will involve a population consisting of per-protocol subject analysis and intention-to-treat analysis. We will adopt a repeated measures design approach to compare the treatment outcomes (MoCA, MMSE, and ADAS-cog) over time between 2 groups. The model will be built to distinguish the intervention effect and the time effect. Among-group differences at each assess time point will be further tested by student *t* test. Categorical variables, containing categorical baseline variables and incidence of AEs, will be analyzed by a chi-square (χ^2^) or Fisher exact test.

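### Section 2.19 permits one-sided and two-sided tests at the same 0.05 level without assigning either to any comparison, the primary MoCA comparison included

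*Protocol article*

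**What the plan says.** The opening sentence of section 2.19 (Statistical analysis) reads "The statistical tests involved in this study will include unilateral and bilateral tests with a significance level of alpha = 0.05". The rest of the section names a repeated-measures approach for MoCA, MMSE and ADAS-cog, Student t tests between groups at each time point, and chi-square or Fisher exact tests for categorical variables. None of these is given a side or a direction.

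Section 2.13 (Sample size) uses MoCA as the main outcome. It says "The test level was set at *α* = 0.05 and *β* = 0.1" and concludes that "the required sample size of each group was 13 cases, and 26 cases in both groups". It does not state sidedness.

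Section 2.20 (Handling of missing data) refers to 95% confidence intervals, but only within its rules for missing values. The article has no general rule that ties the reported interval to the test.

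**The concern.** The plan is not merely silent on sidedness. It authorises both kinds of test at one level and leaves the assignment open. At the same nominal 0.05, a one-sided test sets a lower bar for a favourable claim than a two-sided test.

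The primary outcome is where this matters most. A MoCA difference in favour of acupuncture with a two-sided p between 0.05 and 0.10 could be reported as significant or not significant, and both reports would comply with the text. If it were reported as significant, the 95% confidence interval beside it would include zero, so the test and the interval would disagree. A reader could not tell whether the side had been fixed before or after the result was known.

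**Working it through.** **Inputs.** All are from section 2.13, except the statement on tests, which is from section 2.19.

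- MoCA change: "in the conventional rehabilitation group (without acupuncture) was 2.83 ± 1.13" and "that of MoCA between pre-therapy and posttherapy in acupuncture group was 1.33 ± 1.20"
- α = 0.05 and β = 0.1, so power is 90%
- Stated result: 13 per group
- Loss: "considering that the follow-up loss rate is 20%, the sample size should be 26/(1 – 0.2) = 33 cases"
- Final size: "expand the sample size to a total of 50 cases, 25 cases in each group"

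**Step 1: reproduce the plan's figure.**

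Absolute difference δ = 2.83 − 1.33 = 1.50. Pooled variance = (1.13² + 1.20²)/2 = (1.2769 + 1.4400)/2 = 1.3585, so SD = 1.1655.

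Normal formula: n per group = 2·SD²·(z_α + z_β)²/δ².

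- Two-sided 0.05: 2 × 1.3585 × (1.960 + 1.282)²/2.25 = 12.69, so 13. This matches the stated figure.
- One-sided 0.05: 2 × 1.3585 × (1.645 + 1.282)²/2.25 = 10.34, so 11.

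Noncentral t with the same inputs:

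- Two-sided 0.05: 14 per group (power 0.906; with 13 it is 0.882)
- One-sided 0.05: 12 per group (power 0.920; with 11 it is 0.898)

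Of these four, only the two-sided normal calculation returns 13. It suggests a two-sided design but does not establish one. Then 26/0.8 = 32.5, rounded up to 33, as stated.

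**Step 2: error rates for one comparison.**

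| Rule | False claim in the favourable direction | Total type I error |
|---|---|---|
| Two-sided 0.05 | 0.05/2 = 2.5% | 5% |
| One-sided 0.05, direction fixed in advance | 5% | 5% |
| One-sided 0.05, side chosen to follow the data | 5% | 2 × 5% = 10% |

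**Step 3: what this means on the MoCA scale.**

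With 25 per group, df = 48. The critical t is 2.011 two-sided and 1.677 one-sided. If the sizing SD holds, SE = 1.1655 × √(2/25) = 0.330 points.

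- One-sided threshold: 1.677 × 0.330 = 0.55 points
- Two-sided threshold: 2.011 × 0.330 = 0.66 points

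A favourable difference of 0.60 points, for example, gives t = 0.60/0.330 = 1.82, one-sided p = 0.037 and two-sided p = 0.075. Its 95% confidence interval is 0.60 ± 0.66, or −0.06 to 1.26. It is significant under one permitted test, not under the other, and the interval includes zero.

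**Step 4: power if every test is two-sided at 0.05.**

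- 25 per group: 99.5% (normal) or 99.4% (t)
- 20 per group (25 × 0.8, after 20% loss): 98.3% (normal) or 97.8% (t)

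Even the larger t-based requirement, 28 in total, becomes 28/0.8 = 35 after loss, well below 50.

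**The case against.** The strongest reply has three parts. First, this is a pilot. The numerical rules in Table 3 for going ahead rest on completion and drop-out rates, not on a MoCA p-value. Second, the sentence also permits two-sided tests, so a two-sided primary analysis would comply with it fully. Third, the article condenses a fuller plan, which may assign a side to each test. All three points limit the consequence. They do not justify a sentence that affirmatively allows both kinds of test at one level, and MoCA is still named as the primary outcome and tested.

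Several stronger readings are tempting, and the documents do not support them:

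- **That section 2.19 contradicts a two-sided sample size.** Section 2.13 never says two-sided. That is an inference from the match to 13, and a two-sided t calculation gives 14. Even if the sizing was two-sided, section 2.19 permits two-sided tests.
- **That one-sided testing doubles the false-positive rate outright.** A one-sided test with its direction fixed in advance keeps a total error of 5%. Only the favourable-direction error doubles.
- **That error over the three post-baseline MoCA visits exceeds 20%.** Simulation of three equally correlated normal statistics (assumed correlation 0.7 to 0.5; 1,000,000 draws) gives 20.5% to 23.6% if the side follows the data. With a fixed one-sided rule it gives 10.2% to 11.8%, no higher than the 10.9% to 12.5% for two-sided tests. Testing at several visits is also a separate matter.
- **That harm would be missed.** Section 2.19 assigns adverse-event incidence to chi-square or Fisher exact tests, and nothing says these will be one-sided.

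**Conclusion.** The point stands as an open choice in the analysis rule. Section 2.19 allows one-sided and two-sided tests at 0.05 and fixes neither the comparison nor the direction. For any comparison tested one-sided, the favourable-direction error is 5% instead of 2.5%. Total error reaches 10% only if the side is picked after seeing the data. On MoCA with 25 per group, the results affected are those with t between 1.677 and 2.011, or about 0.55 to 0.66 points if the SD of 1.1655 from the sizing applies.

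The sizing does not settle the intended side, although a two-sided normal calculation reproduces it. Nor does it supply a usable direction: as printed, the larger MoCA change (2.83 against 1.33) belongs to the group without acupuncture. A two-sided sample size is indifferent to that order, but a one-sided test is not, so the labels should be checked.

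This is a free improvement. It does not invalidate the design.

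**What to change.** Replace the first sentence of section 2.19 with: *All tests are two-sided with alpha = 0.05, and treatment effects are reported with 95% confidence intervals.* The word for one-sided tests (unilateral) goes. The test and the reported interval then always agree.

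If the sponsor wants a one-sided test for a particular comparison, that comparison and its direction should be named in advance and tested at 0.025. This gives the same required n as two-sided 0.05.

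The cost is one sentence. No patients, visits or data are added, and the planned 50 stays as it is.

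### The visit-by-visit Student t tests cannot use baseline MoCA or the stratification factor, so run on raw scores they give up precision that an adjusted model would keep

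*Protocol article*

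**What the plan says.** Three sections of the protocol article bear on this.

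- **Sample size (2.13).** The calculation uses change in MoCA from before to after treatment: "the difference of MoCA between pre-therapy and posttherapy in the conventional rehabilitation group (without acupuncture) was 2.83 ± 1.13". The arm labelled acupuncture is given a mean change of 1.33 with SD 1.20. The method was "By comparing the differences between 2 independent samples", and "The test level was set at *α* = 0.05 and *β* = 0.1". The result is 13 per group, 26 in total. Allowing for 20% loss makes 33, and the trial then plans 25 per group.
- **Randomization and allocation concealment (2.14).** Allocation is stratified: "The stratified random allocation operation of experimental group and control group will be completed by the researcher". The factor is not named.
- **Statistical analysis (2.19).** MoCA, MMSE and ADAS-cog are compared over time between groups by a repeated-measures approach, of which the section says: "The model will be built to distinguish the intervention effect and the time effect". It continues: "Among-group differences at each assess time point will be further tested by student" t test.

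Baseline MoCA is collected, and it is one of four MoCA assessments: baseline, 12 weeks, and 3 and 6 months after treatment (2.1 and Table 1).

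**The concern.** The t test is the only between-group comparison that 2.19 names for a particular visit, so as written it supplies the week-12 MoCA difference. A two-sample t test has no place for a baseline score or a stratum. The section does not say whether it is run on raw scores or on change. If on raw scores, the analysis is a different comparison from the one that was sized, and it leaves unused a baseline value that every participant provides.

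What is at stake is precision. This pilot is meant to inform a larger trial, so the width of the interval around the week-12 difference matters at least as much as its p-value. With 25 per arm, chance differences in baseline MoCA are not small, and part of them carries into an unadjusted week-12 difference.

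**Working it through.** **Inputs from the document.** SDs of change 1.13 and 1.20; difference in mean change 2.83 − 1.33 = 1.50 points in absolute value; α = 0.05; β = 0.1; 25 per arm; 20% loss, which leaves 25 × 0.8 = 20 completers per arm.

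**Assumptions.** ρ is not given; the range 0.3 to 0.8 is assumed. Variance is taken as equal at baseline and week 12. Tests are two-sided. Section 2.19 allows both kinds ("The statistical tests involved in this study will include unilateral and bilateral tests with a significance level of alpha = 0.05"), but the two-sided form is the one that reproduces the stated sample size.

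**Step 1: the plan's own figure.** Pooled SD of change = √((1.13² + 1.20²)/2) = 1.166. By the normal approximation, n = 2 × (1.960 + 1.282)² × 1.166² / 1.50² = 12.7, so 13 per group. The stated figure reproduces, which confirms that the trial was sized on change. With 20% loss, 26/0.8 = 32.5, so 33.

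(As worded, 2.13 gives the larger gain to the group without acupuncture. This does not affect n, but the labels need reconciling.)

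**Step 2: SDs for the three possible analyses.**

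- Change: 1.166 at every ρ, since this is the sizing input.
- Raw week-12 score: 1.166 / √(2(1 − ρ)).
- Baseline-adjusted: raw SD × √(1 − ρ²).

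**Step 3: power and precision.** Power is from the noncentral t with 20 per arm and an effect of 1.50. The 95% CI half-width is 2.024 × SD × √(2/20), where 2.024 is the t quantile on 38 degrees of freedom; the one degree of freedom spent on baseline is ignored.

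| ρ | SD raw | SD adjusted | 1 − ρ² | Power raw | Power change | Power adjusted | Half-width raw | Half-width adjusted |
|---|---|---|---|---|---|---|---|---|
| 0.3 | 0.985 | 0.940 | 0.91 | 99.7% | 97.8% | 99.8% | 0.63 | 0.60 |
| 0.5 | 1.166 | 1.009 | 0.75 | 97.8% | 97.8% | 99.6% | 0.75 | 0.65 |
| 0.6 | 1.303 | 1.042 | 0.64 | 94.4% | 97.8% | 99.3% | 0.83 | 0.67 |
| 0.7 | 1.505 | 1.075 | 0.51 | 86.7% | 97.8% | 99.0% | 0.96 | 0.69 |
| 0.8 | 1.843 | 1.106 | 0.36 | 70.8% | 97.8% | 98.7% | 1.18 | 0.71 |

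The adjusted analysis is the most precise in every row. Raw and change scores are equally precise at ρ = 0.5; above that, raw is worse.

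**Step 4: chance baseline imbalance.** With 25 per arm, the standard error of the baseline difference is raw SD × √(2/25): 0.33 points at ρ = 0.5, 0.43 at 0.7 and 0.52 at 0.8. The expected carry-over into the raw week-12 difference is ρ times that: 0.17, 0.30 and 0.42 points.

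**Step 5: the stratification factor.** No figure can be computed, because neither the factor nor its relation to MoCA is given.

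**The case against.** **The main model may already use baseline.** A reader might infer from 2.19 that the repeated-measures model leaves baseline out. The document does not show that. Baseline is one of the four MoCA visits. If it enters as a repeated measure and the effect is read from a group-by-time contrast, it is used, with power of about 99.8% at 20 per arm under compound symmetry and a constant post-treatment effect. Covariate lists are also commonly left to an analysis plan, which is not shown here. This stands in full for the model. It does not cover the t test, which is stated and cannot take covariates.

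**Planned power is not lost at ρ = 0.5.** A reader might infer that the planned 90% fails for raw scores once ρ exceeds 0.5. That value is only where raw and change scores have equal variance. The trial enrols 25 per arm, not 13. For 1.5 points, raw-score power stays at or above 90% up to ρ of about 0.66 with 20 per arm, and about 0.73 with 25.

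**Dilution of the effect is conjecture.** If the treatment effect were a group main effect averaged over all four visits, a sustained 1.5 points would shrink to 1.5 × 3/4 = 1.125. Nothing in 2.19 says that the effect is read that way, and separate tests at each visit point away from it.

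**An unadjusted randomised comparison is not biased.** This is correct. Chance imbalance carries over only by the factor ρ and is already reflected in the standard error. The issue is precision.

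**The t test might be run on change.** The section does not exclude it. Power would then be 97.8% at 20 per arm, and the adjusted analysis would still be somewhat better.

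**Conclusion.** The point holds in a limited form. Section 2.19 fixes a test for visit differences that cannot use baseline MoCA or the stratification factor, in a trial sized on change and randomised in strata. If that test is run on raw scores, the result is valid but less precise than it need be.

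The size of the loss depends on ρ. It is negligible at 0.3. At 0.7 it is clear: half-width 0.96 against 0.69 points, power 86.7% against 99.0%. At 0.8 it is large: 1.18 against 0.71 points, 70.8% against 98.7%. These figures rest on the assumed ρ, equal variances, two-sided testing, 20 completers per arm and the 1.5-point effect from 2.13. The gain from the stratification factor cannot be quantified.

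The document does not settle whether the repeated-measures model includes baseline or which of its contrasts is the treatment effect. Neither an omission of baseline from that model nor a general failure of planned power can be claimed. This is an improvement that should be made, not a threat to validity.

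**What to change.** In 2.19, replace the visit-by-visit t tests for MoCA, MMSE and ADAS-cog. Take the group difference at each post-baseline visit from one repeated-measures model per outcome, with group, visit and group-by-visit, adjusted for the baseline score and the randomisation stratification factor. Name the week-12 adjusted MoCA difference, with its 95% CI, as the treatment effect, and name the stratification factor so that it can be fitted.

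The cost is analysis wording only. Baseline scores are already collected and the strata are known from randomisation; no visit, measurement or participant is added.
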